### Outcomes

#### Primary outcome

The primary outcome is to assess the incidence of prolonged grief of relatives 6 months after the patient’s death in a palliative care unit.

#### Measure of the primary outcome

The intensity of grief reactions is evaluated with the French validated version of the IGC (Inventory of Complicated Grief) [21–23], the most commonly used assessment tool for complicated grief. It was developed by PRIGERSON et al [23] and focuses on symptoms that are distinguishable from symptoms of depression and anxiety. Moreover, the ICG was designed to distinguish between normal reactions and more pathological forms of grief. It consists of 19 first-person statements (such as “Ever since he/she died, it is hard for me to trust people”). Each item is rated from 0 (not at all) to 4 (severe). We defined complicated grief with an IGC scores > 25 (0 best-76 worst). No published minimal clinically difference was reported for the IGC.

#### Prespecified secondary outcomes

Anxiety and depression symptoms in relatives between day 3 and day 5 after patient admission in a palliative care unitAnxiety and depression symptoms in relatives 6 months after patient’s deathPost-traumatic stress disorder symptoms in relatives 6 months after patient’s deathRisk factors for prolonged griefReport of the relative’s grief experience in those who have signs of prolonged grief

#### Measure of the prespecified secondary outcomes

Prespecified secondary outcomes (anxiety, depression, post-traumatic stress disorder symptoms and exploration of relatives’ experience during hospitalization) will be explored during a telephone interview performed by a psychologist specifically used for approaching grieving relatives.

Anxiety and depression syndrome will be evaluated based on The Hospital Anxiety and Depression syndrome (HADS) [19] score, range 0 (best)- 42 (worst). The HADS is valid and reliable, easy to administer, and has been successfully used to measure symptoms of anxiety (HADS-subscale Anxiety) and depression (HADS-subscale Depression) in relatives of palliative care patients [24]. Significant anxiety and depression symptoms will be defined by a score > 8 for anxiety and depression subscales. The minimal clinically important difference is 2.5 for each subscale [25].

Post-traumatic stress disorder symptoms will be evaluated in relatives at 6 months as measured by the Impact Event Scale-Revised questionnaire (IES-R). The IES-R is a valid and reliable scale that has been used successfully in family members of palliative care patients [26]. The instrument contains subscale items on intrusion, avoidance and hyperarousal. We define significant post-traumatic stress disorder symptoms by an IES-R score > 22 (range 0 best-88 worst) [27, 28]. We did not identify any published definition of the minimal clinically important difference for the IES-R on the 0–88 scale.

Risk factors of prolonged grief will be explored through the center, patient and family characteristics. Exploration of relative’s experience during the palliative care hospitalization will be assessed with the FAMI-LIFE questionnaire (12 questions), specifically built for the study by the scientific committee. It reports data about communication features between healthcare clinicians and relatives, information about the last moments of life, and relatives’ needs after death.

### Sample size justification

Prolonged grief reactions were reported in 24.4% [10] at 8 months, and 25.4% [31], 28.6% [15], 30% [32], and 40% [33] at 6 months. We anticipated an incidence of prolonged grief of 25% 6 months after patient death. Horowitz et al reported that the frequency of grief symptoms declined within 6 to 12 months after the bereavement [34]. Grief reactions decreased as a function of time from death with a steepest decrease from the first month to the sixth month after death, and without any significant decrease from 6 months to 13 months [33, 35]. For the current study, we selected a time period of 6 months after the death. According to the medical knowledge, longitudinal studies of relatives at 6 months usually report a participation rate around 60%. To detect the risk factors associated with a prolonged grief with an odd ratio of 2, an alpha risk of 0.05 and a power of 0.80, we anticipate that 500 decedents and their relatives are necessary (assuming the independence of prolonged grief in the relatives of the same family).

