**Methods:**

This is a prospective observational multicenter mixed study. Relatives of adult patients with a neoplasia expected to be hospitalized more than 72 h in a palliative care unit for end-of-life issues will be included within 48 h after patient admission. End-of-life issues are defined by the physician at patient admission. Relatives who are not able to have a phone call at 6-months are excluded. The primary outcome is the incidence of prolonged grief reaction defined by an ICG (Inventory Complicate Grief) > 25 (0 best-76 worst) at 6 months after patient’ death. Prespecified secondary outcomes are the risk factors of prolonged grief, anxiety and depression symptoms between day 3 and day 5 and at 6 months after patients’ death based on an Hospital Anxiety and Depression score (range 0–42) > 8 for each subscale (minimal clinically important difference: 2.5), post-traumatic stress disorder symptoms 6 months after patient’ death based on the Impact of Events Scale questionnaire (0 best-88 worst) score > 22, experience of relatives during palliative care based on the Fami-Life questionnaire, specifically built for the study. Between 6 and 12 months after the patient’s death, a phone interview with relatives with prolonged grief reactions will be planned by a psychologist to understand the complex system of grief. It will be analyzed with the Interpretative Phenomenological Analysis. We planned to enroll 500 patients and their close relatives assuming a 25% prolonged grief rate and a 6-month follow-up available in 60% of relatives.

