### Statistical analysis plan

Patient, relatives and center-variables are reported as numbers (percentage) for qualitative data and medians (Q1–Q3) for quantitative data. For continuous variables, we perform tests of logit linearity and transformation if necessary. Strategy of imputation of missing values will be adapted according to the pattern of missing values. The missing data will be considered by a simple imputation method in case of low frequency (less than 2%) or by multiple imputation if the frequency is higher. Variables with more than 30% missing data will not be included in the analysis. No imputations will be performed for patient outcomes. The primary outcome is the incidence of relatives with an IGC score > 25. The incidence rate will be defined by the ratio between the number of persons who have a prolonged grief on the number of person-time in the study. A 95% Wald confidence interval will be computed for the incidence rate.

To assess the risk factors for prolonged grief in patients’ relatives, multivariable hierarchical logistic regression model will be performed, with a random effect on the center. An univariable analysis will be first performed to select the variables associated to the outcome with a *p*-value threshold of 0.2 to account for the main confounding factors. The relative effect can be considered either as a random effect or a fixed effect in the model. We will then perform multivariable logistic or negative-binomial models for the modification of anxiety, depression and PTSD scores for the secondary criteria. To account for the rate of lost-to-follow-up within the relatives, a weighting on the inverse probability of censoring weight (IPCW) will be performed. All statistical analyses were performed using the SAS software (SAS 9.4, SAS Institute, Cary, NC). A *p* value < 0.05 will be considered significant.

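### The 80% power at an odds ratio of 2 is stated for risk factors in general, but at the design's basis of about 300 analysed relatives it does not hold for factors that are constant within a unit

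*Protocol article*

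**What the plan says.** The section Sample size justification sizes the study on the risk-factor analysis at 80% power. The sentence begins "To detect the risk factors associated with a prolonged grief with an odd ratio of 2, an alpha risk of 0.05 and a power of" and, after giving that figure, concludes that "we anticipate that 500 decedents and their relatives are necessary". The outcome rate comes from the same section: "We anticipated an incidence of prolonged grief of 25% 6 months after patient death". The abstract repeats the basis as "assuming a 25% prolonged grief rate and a 6-month follow-up available in 60% of relatives". The only statement about clustering is that relatives of one family are taken as independent. No term for centre appears, and the power figure is not restricted to any kind of factor.

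Three other places bear on this:
- Measure of the prespecified secondary outcomes: "Risk factors of prolonged grief will be explored through the center, patient and family characteristics".
- Data collection, Center characteristics: a long list of unit descriptors, among them hospital type, bed numbers, staffing ratios, rooms for relatives and visiting policy.
- Statistical analysis plan: a "multivariable hierarchical logistic regression model will be performed, with a random effect on the center".

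**The concern.** A unit descriptor takes the same value for every relative in that unit. In a model with a random centre effect, the precision of its coefficient is limited by the number of units as well as by the number of relatives. A calculation that treats relatives as independent ignores this, so a single power figure cannot describe both unit-level and relative-level factors unless it has room to spare.

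Unit organisation is what the Discussion wants to inform: it notes that teams differ in how they manage grieving relatives and that data on these practices are lacking. If a unit practice shows no significant association, a reader who holds the stated 80% against it may conclude that the practice makes no difference, when the study may have had clearly less power to see it.

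**Working it through.** **Inputs from the article.** Rate 25%, odds ratio 2, alpha 0.05, power 0.80, 500 decedents, 60% follow-up.

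**Assumptions.** Two-sided test; exposure split 50:50; 25% is the rate in the unexposed. The number of centres J and the ICC are not in the text at hand, so J = 10 to 40 and ICC = 0.02 and 0.05 are shown as a range.

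**Step 1: reproduce the 500.**
- Exposed odds = 2 × 0.25/0.75 = 0.667, so the exposed rate is 0.667/1.667 = 40%.
- n per group = [1.96·√(2 × 0.325 × 0.675) + 0.842·√(0.25 × 0.75 + 0.40 × 0.60)]² / 0.15² = 151.9, rounded up to 152; total 304.
- 304/0.60 = 507, close to 500.
- In the other direction, 500 × 0.60 = 300 analysed at one relative per patient. Power at 300 is 79.5% with the pooled-variance formula and 80.2% with the unpooled one.

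The 500 is therefore what independent observations give, and no margin is left for a design effect.

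**Step 2: add centre clustering for a unit-level factor.** Half of the centres are exposed and centres are of equal size.
- Design effect = 1 + (N/J − 1) × ICC; effective N = N / design effect.
- Noncentrality = 0.15 / √[(0.1875 + 0.24) / (effective N / 2)], tested against t on J − 2 degrees of freedom.

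Example with N = 300, J = 20, ICC 0.05: design effect = 1 + 14 × 0.05 = 1.70; effective N = 176.5; noncentrality = 0.15/√(0.4275/88.2) = 2.15; power on 18 df = 53%.

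| Relatives analysed | ICC | 10 centres | 20 | 30 | 40 |
|---|---|---|---|---|---|
| 300 | 0.02 | 50% | 65% | 70% | 73% |
| 300 | 0.05 | 35% | 53% | 62% | 66% |
| 450 | 0.02 | 60% | 78% | 84% | 86% |
| 450 | 0.05 | 40% | 62% | 72% | 78% |
| 600 | 0.02 | 66% | 85% | 90% | 93% |
| 600 | 0.05 | 42% | 67% | 78% | 84% |

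The rows for 450 and 600 stand for 1.5 and 2 analysed relatives per patient (1.5 × 300 and 2 × 300), with relatives of one family treated as independent.

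**Step 3: sensitivity to the test.** A normal approximation without the t correction gives, at N = 300, 60-75% for ICC 0.02 and 42-68% for ICC 0.05 over 10 to 40 centres. All of these stay below 80%.

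**Step 4: simulation at N = 300.** With 1,000 runs per setting, ICC on the logit scale and a t-test on centre proportions, power for a unit-level factor with 10, 20 and 30 centres was 49%, 66% and 70% at ICC 0.02 and 41%, 57% and 62% at ICC 0.05. A factor that varies within centres, tested by a centre-stratified test, kept 75-79% at these ICCs, against 76-79% at ICC 0. The shortfall is thus specific to factors that are constant within a unit.

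**The case against.** The strongest reply is that the recruitment section allows every relative present to be included, so more than 300 relatives may be analysed. This stands in part. With 450 relatives at ICC 0.02, power reaches 84% with 30 centres and 86% with 40; with 600 it is 85% at 20 centres. But the sample size section claims no such offset, gives no expected number of relatives per patient, and these gains depend on its assumption of independence within families. With 10 centres no cell of the table reaches 80%.

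Second, the number of centres and the ICC are not known here, and the Discussion speaks of a large set of centres, which makes the 10-centre column less likely. This bears on the size of the loss. It does not change the direction at 300 relatives.

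Third, some practices of interest are not purely unit-level. Condolence letters and bereavement follow-up appear among the centre characteristics, but Table 3 (items 7 and 8) also asks each relative about them. As reported by relatives they can vary within a unit and are little affected. Hospital type, staffing ratios, facilities and visiting rules remain constant within a unit.

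Fourth, risk factors are a secondary outcome described as explored, and an article may leave an ICC to the full protocol. True, but they are the stated basis of the sample size, and the point is an unrestricted power figure that the article does state, not a missing detail. Nothing in the text says that a null result for a unit practice would be read as absence of effect; that is a risk of misreading, not a planned inference.

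**Conclusion.** The point holds in a limited form. The 500 is not miscalculated: it is reproduced under independence. What is not supported is its extension to all risk factors. At the design's basis of about 300 analysed relatives there is no margin, so any positive centre ICC puts a unit-level factor below 80%: about 50-73% at ICC 0.02 and 35-66% at ICC 0.05 for 10 to 40 centres. These figures rest on an assumed ICC, number of centres, even split and equal centre sizes.

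A reader might go further and infer that 80% power is unattainable for centre factors, that true power is well below it, or that only the number of units matters. The documents do not support this. Several relatives per patient are allowed, and with 450 relatives the range is 60-86% at ICC 0.02 and 40-78% at ICC 0.05. The number of relatives does count: with 30 centres at ICC 0.05, going from 300 to 600 raises power from 62% to 78%.

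**What to change.** In Sample size justification:
1. Limit the statement of 80% power at an odds ratio of 2 to factors that vary within centres.
2. Add the power, or the detectable odds ratio, for factors that are constant within a unit, at the actual number of centres, the expected number of analysed relatives and a stated ICC range (for example 0.02 to 0.05). If several relatives per patient are counted on, say so, and say that this relies on independence within families.
3. Label unit-level associations exploratory, report them with confidence intervals, and state that non-significance is not taken as absence of effect.

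The cost is some wording and one calculation, with no added patients. The downside is a less favourable stated power for unit-level factors.

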### Statistical analysis plan

Patient, relatives and center-variables are reported as numbers (percentage) for qualitative data and medians (Q1–Q3) for quantitative data. For continuous variables, we perform tests of logit linearity and transformation if necessary. Strategy of imputation of missing values will be adapted according to the pattern of missing values. The missing data will be considered by a simple imputation method in case of low frequency (less than 2%) or by multiple imputation if the frequency is higher. Variables with more than 30% missing data will not be included in the analysis. No imputations will be performed for patient outcomes. The primary outcome is the incidence of relatives with an IGC score > 25. The incidence rate will be defined by the ratio between the number of persons who have a prolonged grief on the number of person-time in the study. A 95% Wald confidence interval will be computed for the incidence rate.

To assess the risk factors for prolonged grief in patients’ relatives, multivariable hierarchical logistic regression model will be performed, with a random effect on the center. An univariable analysis will be first performed to select the variables associated to the outcome with a *p*-value threshold of 0.2 to account for the main confounding factors. The relative effect can be considered either as a random effect or a fixed effect in the model. We will then perform multivariable logistic or negative-binomial models for the modification of anxiety, depression and PTSD scores for the secondary criteria. To account for the rate of lost-to-follow-up within the relatives, a weighting on the inverse probability of censoring weight (IPCW) will be performed. All statistical analyses were performed using the SAS software (SAS 9.4, SAS Institute, Cary, NC). A *p* value < 0.05 will be considered significant.

To describe the experience of bereaved relatives through an interview, a purposive subset of relatives will be selected. We will comply with the recommendations regarding purposive sample in Interpretative Phenomenological Analysis [29]. This sample will be purposive with heterogenous characteristics. According to the IPA guideline, participation of at least 15 people will allow a broad and relevant understanding of the meaning-making process of the grief experience. To maximize the meaning making heterogeneity, we plan to recruit women and men, from various palliative units, from various geographical areas, of various ages, and with various types of relationship with the deceased. We will stop the recruitment when the adequate variety of meaning making processes will be obtained.

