## Discussion

This study will depict the grieving process of relatives after patient ‘s death in palliative care in France. According to the World Health Organization definition of palliative care, providing support for the relatives during their grieving process is an inherent part of palliative care services [36]. Currently, there is no consensus to which type and amount of support is indicated to meet the demand of the WHO definition of bereavement support in palliative care [37]. There are hardly substantial pieces of knowledge on how bereavement of relatives of palliative care patients is handled. The need for support in the bereavement period was poorly predicted by the healthcare clinicians [33]. Having baseline data of the incidence rate of prolonged grief and other psychological consequences, of risk factors of relative’s prolonged grief, and better knowledge of the management of end-of-life issues in palliative care units will increase our knowledges on the grieving process. Currently, palliative care team have different strategies for managing grieving relatives. No scientific data are available on these practices, and there are no national guidelines with a sufficient high grade of proofs.

The strengths of this study will be the high number of relatives included, and the multicenter design with the recruitment of patients from a large set of centers with patient’s characteristics consistent with those of patients usually admitted in palliative care in France, which will ensure that results could be generalized. The mixed design will enable to approach how relatives experience the period of bereavement and to help healthcare clinicians in targeting interventions to decrease bereaved relative’s burden.

This study will have several limitations. First, the exploration of psychological consequences will focus on patients with neoplasia, who do not represent all the case-mix of patients admitted in palliative cares. Second, evaluation will be performed at only one time-point, which is insufficient to describe the evolution of the grieving process. We choose one point to limit the rate of lost-to-follow-up among relatives. Third, the centers are all in France, and the study results might not be generalized to other countries.

Our study is part of a scientific approach to the management of grief in palliative care to build a scientifically valid management program.

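### The primary estimate is defined as cases per person-time, but prolonged grief is a yes/no status read once at 6 months, so the rate does not estimate the planned proportion

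*Protocol article*

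**What the plan says.** The abstract of the protocol article sets the outcome: "The primary outcome is the incidence of prolonged grief reaction defined by an ICG (Inventory Complicate Grief) > 25", taken at 6 months after the death. Table 1 and the section on the organization of the study place the ICG in a single telephone call at that time. The Discussion confirms that "evaluation will be performed at only one time-point".

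The Sample size justification plans on a percentage: "We anticipated an incidence of prolonged grief of 25% 6 months after patient death". The published results listed beside it (24.4%, 25.4%, 28.6%, 30% and 40%) are percentages too.

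The Statistical analysis plan section first names the outcome as the incidence of relatives above the ICG cut-off, then defines the estimate: "The incidence rate will be defined by the ratio between the number of persons who have a prolonged grief on the number of person-time". The denominator is qualified only as time in the study. The section adds: "A 95% Wald confidence interval will be computed for the incidence rate". It gives no start, stop or unit for the person-time, and no rule for the time of relatives who are never reached. The same section models the same outcome by logistic regression and plans inverse probability of censoring weighting (IPCW) for loss to follow-up.

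**The concern.** A person-time rate needs events that occur at observed, or at least bracketed, times among people followed while at risk. Here each relative has one reading at one time. Nobody's onset is dated. The Sample size justification itself reports that grief reactions decline most steeply between the first and the sixth month, so a relative who was above the cut-off early and then recovered is not counted. What the call yields is the share of relatives above the cut-off at 6 months.

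Dividing that count by person-time gives a figure in different units from the planned 25% and the cited percentages. It can also move with features unrelated to grief, depending on how time in the study is read. Relatives enter before the death ("will be included within 48 h after patient admission"), so the time from entry to the call includes a stay of variable length. Calls may be repeated up to five times before a relative is declared lost. At stake is the number the study will report as its primary result, and whether two analysts following the same sentence would report the same one.

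**Working it through.** **The plan's own figures.** An odds ratio of 2 on a risk of 25% moves the odds from 0.25/0.75 = 0.333 to 0.667, a risk of 40%. Comparing 25% with 40% in two equal groups (two-sided alpha 0.05, power 0.80, no continuity correction) needs 304 relatives with data. With 60% participation, 304/0.60 = 507, close to the stated 500. This assumes a risk factor present in half the relatives, 25% as the risk in the unexposed, and one analysed relative per patient. The stated sample size is therefore reproduced with prolonged grief as a binary status and 25% as a proportion; person-time plays no part.

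**Inputs for the comparison.**
- From the document: 500 patients, 60% participation, 25% prolonged grief.
- Assumed: one relative per patient (the recruitment section allows more), giving 500 × 0.60 = 300 assessed, 300 × 0.25 = 75 cases and 200 not assessed.
- Assumed: a stay between inclusion and death of 10 to 40 days. The document gives no length of stay.

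**Proportion at 6 months.** 75/300 = 25.0%. Standard error √(0.25 × 0.75/300) = 0.025. 95% Wald interval 0.25 ± 1.96 × 0.025 = 20.1% to 29.9%.

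**Rate, by reading of time in the study**

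| Reading | Person-years | Cases per person-year |
|---|---|---|
| Assessed relatives, exactly 6 months from death | 300 × 0.5 = 150 | 75/150 = 0.50 |
| Assessed relatives, from inclusion, 10-day stay | 300 × (182.6 + 10)/365.25 = 158.2 | 0.474 |
| Assessed relatives, from inclusion, 40-day stay | 300 × (182.6 + 40)/365.25 = 182.8 | 0.410 |
| From death, 200 unreached relatives credited 1 month each | 150 + 200/12 = 166.7 | 0.450 |
| From death, 200 unreached credited 3 months each | 150 + 50 = 200 | 0.375 |
| From death, 200 unreached credited 6 months each | 150 + 100 = 250 | 0.300 |

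The number of cases and the number assessed are the same in every row. In the first row, 0.50 × 0.5 year returns 25%. In the second and third, multiplying by half a year gives 23.7% and 20.5%, although the observed share is still 25%.

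**Interval.** The plan says Wald without naming a distribution. If it is the usual Poisson form for a rate, the first row gives 0.50 ± 1.96 × √75/150 = 0.387 to 0.613. Over half a year that is 19.3% to 30.7%, against 20.1% to 29.9%. The ratio of widths is 1/√0.75 = 1.155, so about 15% wider, conditional on the Poisson reading.

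**The case against.** The best defence is that this is one badly worded sentence in a plan that otherwise treats the outcome correctly. The planning value is a percentage, the risk-factor model is logistic, and the count of cases and the number assessed will be collected anyway. If the clock runs from the death to the 6-month call, the rate is the proportion in other units and the 25% can be recovered. All of this stands, and it limits the damage. It does not rescue the sentence, because the denominator is spelled out and nothing in the document restricts it to 6 months from the death.

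Several stronger readings are tempting and are not supported:

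- *That the plan counts the days before death and the time of lost relatives.* The text says only "on the number of person-time in the study". Both are possible readings; neither is stated.
- *That the same data give a twofold range of results.* Reaching about 0.25 per person-year needs a 40-day stay and all 200 unreached relatives credited with time up to 6 months: 75/(500 × 222.6/365.25) = 0.246. The document supports neither input, and any one analysis would apply one definition.
- *That the interval will be about 15% too wide.* This holds only if the unnamed Wald interval is a Poisson one.
- *That the word incidence is wrong.* Each relative's bereavement starts on a known date, so speaking of an incidence proportion at 6 months is defensible. The denominator is the problem.

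**Conclusion.** The estimator is wrong as written. A status read once, with no observed onset, calls for a proportion; the plan specifies a rate on an undefined time base, at odds with its own planning value, comparators and logistic model.

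That conclusion needs no assumption. The size does: with 300 assessed and 75 cases, the harm ranges from nil beyond a change of unit (0.50 per person-year at exactly 6 months from death) to a rate of 0.41 to 0.47 if time starts at inclusion with a stay of 10 to 40 days, and lower if unreached relatives add time. A reader might infer that the primary result will be unusable or that the study is mis-sized. Neither follows: the proportion can be computed from the data to be collected, and the 500 rests on the odds ratio for risk factors.

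**What to change.** In the Statistical analysis plan section, replace the person-time definition and the interval sentence with text to this effect:

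> The primary estimate is the proportion of relatives with an ICG score above 25 at 6 months, among relatives of patients who died in the palliative care unit. It is estimated from the relatives assessed, weighted by the inverse probability of censoring weights planned for loss to follow-up; the unweighted proportion is shown alongside. A 95% confidence interval for a proportion is given, with a variance that allows for several relatives of the same patient.

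The weighting should be named because participation of only about 60% is expected; a definition limited to those assessed could be read as replacing the planned IPCW with an unweighted complete-case figure. The variance clause is needed because all relatives present may be included.

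The cost is a few lines of text. Sample size, recruitment, data collection and the risk-factor models do not change.

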#### Data collection

##### Center characteristics

All data will be collected on an e-CRF built by the ICUREsearch company (Contract Research Organization). Data will be on center, patients and relatives. Palliative care unit characteristics are the following: hospital type (university, community, or private hospital) number of palliative care beds, number of senior physicians and fellows, physician-to-patient ratio, nurse-to-patient ratio (day and night), presence of a waiting room and relative room, availability of a psychologist, physiotherapist, social worker, occupational and music therapist, biographer; availability of interpret or religious services; availability of a dedicated nurse for relative meetings, of volunteers, of speaking group for relatives; time intervals allowed for visit; organization of different meetings (admission, weekly, death period), delivery of an information leaflet at admission and after death, delivery of a children leaflet, delivery of a condolence letter, bereavement follow-up process, availability of a 24-h visitation policy, age for children visitation, possibility for a pet to visit the patient, availability of staying during the night (bed in the patient ‘room, dedicated room, other), and participation in patient care.

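### The 95% Wald interval for the primary incidence is specified with no allowance for clustering by centre or family, so with the default variance it may be too narrow

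*Protocol article*

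**What the plan says.** The Statistical analysis plan section of the protocol article makes the primary outcome one pooled incidence of relatives with a score above 25, defined as the "ratio between the number of persons who have a prolonged grief on the number of person-time in the study". It then states: "A 95% Wald confidence interval will be computed for the incidence rate". Nothing is said there about centre, family or the variance behind the interval.

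The next paragraph turns to risk factors for the same outcome. There a "multivariable hierarchical logistic regression model will be performed, with a random effect on the center", and a relative effect may be taken as random or fixed.

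Four other places bear on the point:

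- Inclusion criteria: every relative present may be enrolled, so one patient can contribute several.
- Sample size justification: relatives of one family are assumed independent. Centre is not mentioned.
- Center characteristics: unit-level practices are recorded, among them "delivery of a condolence letter, bereavement follow-up process, availability of a 24-h visitation policy". The section on measures of secondary outcomes lists centre characteristics among the risk factors to explore.
- Discussion: "the multicenter design with the recruitment of patients from a large set of centers" is given as a strength that allows the results to be generalised.

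**The concern.** Relatives are nested in families and families in palliative care units. Relatives of one patient share the same death. Relatives in one unit share its staff, information practice and bereavement follow-up. Either can make outcomes within a group more alike than outcomes between groups. The risk-factor model makes room for this, and the sentence on the primary interval does not.

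The target of inference matters too. If the estimate is meant to describe palliative care in France and not only the units that took part, the units are a sample and the variation between them belongs in the standard error. An interval that leaves it out would have real coverage below the stated 95%. This affects the only primary result, and readers would take the figure as a national benchmark.

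**Working it through.** **Inputs from the article.** Anticipated incidence 25% ("We anticipated an incidence of prolonged grief of 25% 6 months after patient death"); 500 decedents and their relatives; 6-month follow-up in 60%. Analysed relatives: 500 × 0.60 = 300, taking one relative per decedent.

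**Inputs assumed.** Number of centres J (10, 20 or 30), ICC (0.01 or 0.05) and equal centre sizes. None of these is in the text at hand.

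**The plan's own figure first.** The sample size is set "with an odd ratio of 2, an alpha risk of 0.05 and a power of 0.80". An odds ratio of 2 from 25% gives odds of 1/3 × 2 = 2/3, that is 40%. Comparing 25% with 40% (two-sided, 1:1 exposure; both assumed) needs 152 per group, 304 in all, and 304 / 0.60 = 507. The stated 500 is therefore reproduced to within 1.4%, by a formula that treats relatives as independent and has no centre term.

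**Unadjusted interval.** SE = √(0.25 × 0.75 / 300) = 0.025. Half-width = 1.96 × 0.025 = 4.9 points, giving 20.1% to 29.9%.

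**Centre clustering.** Design effect DE = 1 + (300/J − 1) × ICC. Adjusted half-width = 4.9 × √DE. Coverage of the unadjusted binomial interval = 2Φ(1.96/√DE) − 1.

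| Centres | ICC | DE | Half-width needed (points) | Coverage, binomial | Coverage, Poisson |
|---|---|---|---|---|---|
| 30 | 0.01 | 1.09 | 5.1 | 94% | 97% |
| 30 | 0.05 | 1.45 | 5.9 | 90% | 94% |
| 20 | 0.01 | 1.14 | 5.2 | 93% | 97% |
| 20 | 0.05 | 1.70 | 6.4 | 87% | 92% |
| 10 | 0.01 | 1.29 | 5.6 | 92% | 95% |
| 10 | 0.05 | 2.45 | 7.7 | 79% | 85% |

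Beta-binomial simulation (20,000 runs per setting) gave binomial coverage of 86% for 20 centres and 89% for 30 at ICC 0.05, close to the formula. A centre-level t interval covered 94% to 95% throughout the simulated settings (ICC 0.02 to 0.10).

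**Person-time reading (last column).** The stated definition divides by person-time. With 300 × 0.25 = 75 events and a Poisson variance, the relative half-width is 1.96/√75 = 22.6%, or 0.226 × 25 = 5.7 points on the same scale. The variance ratio to the binomial is 1/(1 − 0.25) = 1.33, so coverage becomes 2Φ(1.96 × √1.33/√DE) − 1. Such an interval is too narrow only when DE exceeds 1.33, that is when ICC exceeds 0.33/(300/J − 1): about 0.011 for 10 centres, 0.024 for 20 and 0.037 for 30.

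**Family clustering alone.** With k relatives per patient and within-family correlation ρ (both assumed), DE = 1 + (k − 1)ρ. For k = 1.5 and ρ = 0.3 it is 1.15. For k = 2 and ρ = 0.5 it is 1.50, and an unadjusted half-width would need to be √1.50 = 1.22 times as wide.

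**The case against.** The strongest reply is that the article never says the observations are treated as independent. Wald fixes the form of the interval, estimate ± z × SE, and not the SE. The remedies proposed here also give Wald-type intervals, so they complete the sentence and do not contradict it. A condensed article may leave the variance estimator to the full protocol. This stands as far as it goes: no independence assumption is stated for this interval. But the article fixes the primary interval, handles centre explicitly in the next paragraph, and assumes independence within families in its sample size. With no cluster term named, the usual software default is the independent-observations variance.

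A reader might infer that the primary and risk-factor analyses assume opposite things about centres. The text does not support that. A random effect permits between-centre variance without asserting its size, and recording unit practices is exploration, not a forecast that outcomes differ.

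A reader might also infer that the interval simply is too narrow. That cannot be shown either. The ICC is unknown and could be near zero, in which case nothing changes. The 10-centre rows fit the description of many centres least well. On the literal person-time definition, the Poisson variance covers modest clustering. That protection is accidental, however: it does not grow with the clustering, and at ICC 0.05 with 20 centres coverage is still about 92%.

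**Conclusion.** The point holds conditionally. As written, the primary interval makes no allowance for clustering that the design builds in at two levels. Family clustering is the better documented of the two, because several relatives per patient are admitted and their independence is assumed in so many words. If the default variance is used, the interval understates uncertainty to the extent that outcomes correlate within centres or families.

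Under the binomial reading with 300 relatives, 25% incidence and one relative per patient, the understatement runs from slight (4.9 against 5.1 points at 30 centres and ICC 0.01) to material (4.9 against 6.4 points at 20 centres and ICC 0.05, with real coverage of 86% to 87%). Several relatives per patient with correlated outcomes would add to it. The documents at hand do not allow one value to be chosen from this range. The change is still worth making, because it costs little whichever value is true.

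**What to change.** Add one sentence to the analysis section that fixes the variance of the primary interval. Either option serves:

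1. A variance clustered on centre as the primary sampling unit (survey-type or GEE sandwich), with t degrees of freedom of centres minus 1. Because families are nested in centres, this also absorbs correlation within families.
2. The marginal proportion from an intercept-only logistic model with the random centre effect already planned plus a family effect. The estimate must be averaged over the random effects, since the back-transformed intercept describes a typical centre and not the population proportion.

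The same sentence should say whether the interval is for a proportion at 6 months or a person-time rate, since the default variance differs, and whether the planned inverse-probability weights apply to it. If they do, option 1 accommodates them.

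The cost is small. No new data are needed, and SAS 9.4, already named, has the procedures (SURVEYFREQ, GENMOD, GLIMMIX). The downside is a somewhat wider interval. The t multiplier adds a little: with 20 centres it is 2.09 in place of 1.96, so 6.4 points become 6.4 × 2.09/1.96 = 6.8. If the ICC is zero, that multiplier is essentially the whole price.
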